To minimise these threats, we are following a modified two-stage consent design [39, 40], as described in the Medical Research Council (MRC) framework for complex interventions [41]. This will hopefully encourage recruitment to and retention in the trial while maintaining participants’ blinding to group allocation. First, we will invite participants to join a study monitoring progression and adjustment to life post stroke and aphasia and comparing different packages of care. Those who consent will be randomised. Those assigned to the control group will receive usual care; they will know that other people may receive different care, against which they will be compared, but they will not know what this entails. The second stage of consent will involve only those participants who have been randomised to peer befriending. A separate visit (conducted within their own home/community setting) will be conducted by the Trial Manager within 1–2 weeks of randomisation to inform participants of their allocation in the intervention arm of the trial, give them information about the peer befriending, and get their consent to participate in this arm. No instances are expected to occur where a participant in the control arm may need to be unblinded.

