Trained peer-befrienders will visit participants in their own home six times (each visit aimed to be at least 1 h) over a period of 3 months. A further two visits within the next 6 months will also be offered for a gradual transition to the end of the peer befriending. Participants will be paired with and introduced to their peer-befriender as soon as possible after and within 1 month of randomisation. If this is not feasible, the reasons for this will be recorded. Where possible, pairing will take account of preferences around gender, cultural factors, age, and personal interests. The schedule and nature of visits will be agreed between the pair at their first meeting. This meeting will also identify possible goals for the intervention. For example, participants might highlight concerns that they would like to discuss or activities that they would like to pursue. Subsequent visits may include conversation, problem-solving, trips out e.g. to a local group, and joint activities.

After each visit peer-befrienders will complete an aphasia-friendly record sheet. This will include whether a visit was cancelled and reason why, length of visit, topics discussed, activities undertaken, any decisions made, and date and time of next visit. Peer befrienders will complete this record sheet immediately or as soon as possible after each visit if necessary with the help of the befriender facilitator who will collate these sheets during monthly supervision sessions. The facilitator will pass the record sheets on to the Trial Manager on a monthly basis.

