All analyses will initially be conducted on an intention-to-treat basis. A second per protocol analysis will be done on the primary and secondary outcomes, excluding participants who are not in compliance with the protocol. Participants deemed not compliant will include those who did not consent at the second stage, completed less than six peer befriending sessions, were found to be ineligible after randomisation based on the inclusion/exclusion criteria, and participants in the usual care group who received peer befriending outside the study as reported to assessors or measured using the CSRI (in addition to their removal, we may explore analysing them in the peer group).

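### The per-protocol rules remove PEER participants for behaviour that only PEER participants can show, so the two arms are differently selected after randomisation and the comparison can be biased in either direction.

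*Protocol article*

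**What the plan says.** Under Outcome measures' analyses, the protocol article puts intention-to-treat first: "All analyses will initially be conducted on an intention-to-treat basis". It then adds: "A second per protocol analysis will be done on the primary and secondary outcomes, excluding participants who are not in compliance with the protocol".

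Four groups count as non-compliant. The first two are given as: "Participants deemed not compliant will include those who did not consent at the second stage, completed less than six peer befriending sessions". The third is anyone in either arm who "were found to be ineligible after randomisation based on the inclusion/exclusion criteria". The fourth is USUAL participants who received peer befriending outside the study. For this last group the text adds an option: "in addition to their removal, we may explore analysing them in the peer group".

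Under Two-stage consent process: "The second stage of consent will involve only those participants who have been randomised to peer befriending". That visit takes place 1-2 weeks after randomisation. USUAL participants know that others may receive different care but are not told what it is.

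Under Intervention arm: "Participants will be paired with and introduced to their peer-befriender as soon as possible after and within 1 month of randomisation". Six visits over 3 months follow. Outcomes are measured at 4 and 10 months.

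**The concern.** Refusing second-stage consent and completing fewer than six visits both happen after randomisation, and both can happen only in PEER. People who decline or stop early may differ from those who continue in mood, fatigue, aphasia severity or how much support they feel they need. Their counterparts in USUAL are never offered befriending, cannot be identified, and stay in the analysis. The retained PEER group is then compared with a USUAL group that still contains its would-be non-adherers, and randomisation no longer protects the contrast.

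Two features add to this. Analysing USUAL participants under PEER would abandon allocation altogether. And the six-visit count may not be complete when the 4-month outcome is taken, so membership of the set analysed at 4 months could depend on later events.

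At stake is a second set of estimates, across all primary and secondary outcomes, that could be read as the effect in people who actually received befriending.

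**Working it through.** **The protocol's own figure.** Under Sample size, 50 participants retained (25 per arm), two-sided alpha 0.05 and an effect size of 0.8 are said to give about 80% power. The normal approximation gives 80.7% and the t-test 79.1%, so the figure reproduces. 0.8 × 3.6 = 2.88, consistent with the stated difference of about 3 points. This point disputes none of these figures.

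**Which arm each exclusion can reach**

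| Exclusion | PEER | USUAL |
|---|---|---|
| No second-stage consent | yes | not possible |
| Fewer than six visits | yes | not applicable |
| Ineligible after randomisation | yes | yes |
| Befriended outside the study | no | yes |

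The two arm-specific sets are chosen on different behaviour, so one does not offset the other.

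**Size of the bias with no true effect.** Let f be the share of PEER removed and g the gap in untreated outcome between those removed and those kept. The PEER mean before exclusion is f × (mean of removed) + (1 − f) × (mean of kept). The kept group therefore differs from the full arm by f × g, and that is the unadjusted bias. The documents give neither f nor g. Assumed ranges are f = 20-40% and g = 0.3-0.8 SD. The SD of 3.6 is from Sample size.

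- Lowest: 0.20 × 0.3 = 0.06 SD; × 3.6 = 0.22 points.
- Highest: 0.40 × 0.8 = 0.32 SD; × 3.6 = 1.15 points.

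**Rejection rate with no true effect** (normal approximation, unadjusted, 25 in USUAL and 25 × (1 − f) in PEER). The standard error in SD units is √(1/n in PEER + 1/25).

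| f | g (SD) | n in PEER | Bias (SD) | SE (SD) | Bias/SE | Rejection |
|---|---|---|---|---|---|---|
| 20% | 0.3 | 20 | 0.06 | 0.300 | 0.20 | 5.5% |
| 40% | 0.3 | 15 | 0.12 | 0.327 | 0.37 | 6.6% |
| 20% | 0.8 | 20 | 0.16 | 0.300 | 0.53 | 8.3% |
| 40% | 0.8 | 15 | 0.32 | 0.327 | 0.98 | 16.5% |

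The sign of the bias follows the sign of g. If those removed would have scored worse, the bias favours PEER; if better, it favours USUAL; if removal is unrelated to outcome, it is zero.

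**Timing.** Pairing at the latest planned point (1 month) plus 3 months of visits is 1 + 3 = 4 months, the time of the first follow-up. Earlier pairing puts the sixth visit before it. If pairing slips beyond a month, which the protocol foresees by asking for reasons to be recorded, the sixth visit can fall after it.

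**The case against.** The strongest reply is that this is a familiar limitation of a secondary analysis. Intention-to-treat comes first, the section labels all between-arm comparisons as exploratory only, and feasibility outcomes take precedence. This stands, and it limits how much the point matters.

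Several stronger readings are tempting, but the documents do not support them.

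- A reader might infer that selected PEER participants are compared with an unselected USUAL arm. USUAL is also selected, because ineligible and outside-befriended participants are removed from it. The arms are differently selected.
- A reader might infer that the bias favours PEER. Entry is restricted to people with low distress, and those who feel well could just as easily decline or stop early. The direction cannot be derived.
- A reader might take the 16.5% as typical. It is the worst corner of assumed ranges, with a gap as large as the whole effect the trial is powered to detect. The other three corners lie between 5.5% and 8.3%.
- A reader might infer that the per-protocol estimate will drive progression. The Discussion refers to effect sizes with confidence intervals alongside acceptability, safety, recruitment and retention, and does not say which analysis set supplies them.
- A reader might infer that the schedule normally runs past the 4-month assessment. As planned it reaches 4 months only at the latest pairing, and the point does not touch the 10-month outcome.

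The model also adjusts for baseline GHQ-12 and for the minimisation factors, which include aphasia severity, so part of any gap would be removed. But its covariates are chosen for imbalance and missingness, not as predictors of adherence, so the remainder is uncontrolled. Finally, the arm-switching option is only tentative.

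What survives is the one-arm exclusion itself. The protocol states it outright, so it is not a detail left to the analysis plan.

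**Conclusion.** The point holds. Followed as written, the per-protocol rule produces a non-randomised comparison, because two of its criteria can remove only PEER participants and no equivalent group can be found in USUAL. Under the assumed 20-40% exclusion and 0.3-0.8 SD gap, the unadjusted bias is 0.06-0.32 SD (0.2-1.2 GHQ-12 points), against a detectable difference of about 3 points, and null rejection is about 5.5% to 16.5%. Baseline adjustment would lower these figures to an unknown extent, and the sign is open. The timing problem is a possibility at the edge of the schedule. The damage is confined to an exploratory second analysis; the intention-to-treat comparison is untouched. The change is worth making because the protocol commits to the rule for all primary and secondary outcomes and the repair is cheap.

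**What to change.** Keep intention-to-treat as the main comparison and change the rest as follows.

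1. Replace the per-protocol estimate with a complier-average causal effect that uses randomised arm as the instrument and keeps everyone randomised.
2. Define exposure as befriending received, for example at least one visit. Count befriending that USUAL participants report to assessors or in the CSRI as exposure too; the intervention database covers PEER only.
3. Use the same baseline covariates as the main model, including predictors of missingness, and state how missing outcomes are handled.
4. Drop the option of analysing USUAL participants in the PEER group.
5. If a per-protocol result is still shown, label it non-randomised and supplementary.

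Session counts and second-stage decliners are already reported as feasibility and fidelity results, so nothing is needed there.

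**Cost.** This is a change of analysis wording, using data already planned for collection. Confidence intervals will be wider at about 50 participants. As a rough guide, the estimate and its interval are divided by the between-arm difference in exposure. If 20-40% of PEER had no visits and nobody in USUAL was befriended, that means widening by 1/0.8 = 1.25 to 1/0.6 = 1.67. The method assumes that allocation to PEER without any visits has no effect, which the Trial Manager's disclosure visit strains somewhat. Its missing-data handling would also differ from the maximum-likelihood mixed model and must be described.

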#### Missing data

The amount and reasons for missing data will be summarised overall and by treatment group. Missing data will be accounted for where mixed models are applied under the missing at random assumption using the maximum likelihood algorithm. The baseline characteristics of those missing follow-up and those with complete follow-up will be summarised and variables affecting missingness will be examined using a logistic predictor of missingness model. This will be done by generating a binary variable for missingness for the primary outcome variable 10 months post-randomisation (we will explore the need to do this either separately or combined for the primary and secondary outcomes) and regressing this on baseline variables. Any variables found to be important predictors of missingness will be included in the primary and secondary outcome models. From a health economic perspective, where there is missing data, we will analyse the data on a complete case analysis basis and additionally use mean imputation for missing values. This will allow for a sensitivity analysis indicating whether missing values could be biasing the data.

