### Sample size

We will recruit in total 60 participants with aphasia (30 in each arm of the study). Allowing for a ~ 15% lost to follow-up rate, at least 50 will complete the study. With 60 participants recruited, we will be able to estimate a 95% confidence interval for the recruitment rate to within approximately 25%. This sample size will be adequate to estimate important parameters needed to inform the design and the sample size of a full trial, such as the standard deviation, consent rates, event rates. This sample size also meets recommended sample sizes for feasibility studies [59].

Although this is a feasibility study, we would like to estimate exploratory differences between the PEER and USUAL arms. If we assume we retain 50 participants at follow-up, a two-sided test, *α* = 0.05, and independence of participants, we will have 80% power to detect an effect size of approximately 0.8. The standard deviation of the primary GHQ-12 outcome in a generic population of patients with stroke has been shown to be approximately 3.6—this was using the 0 0 1 1 scoring, with total scores ranging from 0 to 12 [60]. This effect size corresponds to an approximate mean difference of 3 points between groups. This sample size is sufficient for these exploratory comparisons; however, in a definitive trial, we would want to have higher power to detect a smaller effect size. This feasibility study will give us a standard deviation specific to the group that we would be interested in recruiting for a definitive trial, so would help to inform such a sample size calculation.

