#### Economic evaluation analysis

This pilot economic evaluation study has the objective of detecting problems in the cost collection, exploring how patients respond to the primary outcome in the study, the GHQ-12, and comparing it to the EQ-5D-5 L instrument, as well as developing the economic evaluation model that will be applied to a phase III RCT. The pilot economic evaluation will compare incremental costs to incremental health gains of the PEER arm versus USUAL arm. Due to the very low numbers, this will be strictly an exercise to detect problems in the process of data collection and development of the full economic evaluation model. The rationale is to use the feasibility stage data to prepare a future full trial cost-effectiveness.

For the costs, we will use data collected on the CSRI on service use (including health, social, and voluntary services) and associated costs at 4 and 10 months post-randomisation. Unit costs of resources used will be derived from routine sources locally where possible and from national sources such as the NHS reference costs.

Health gains will be obtained from the answers to both the GHQ-12 and to the EQ-5D-5 L instruments. The gold standard for economic evaluation is to use generic health state outcome measurements because these allow comparability across clinical areas. Thus, we will run two types of pilot economic evaluation analyses. First, we will run a pilot cost-effectiveness analysis based on the GHQ-12. Second, we will perform a pilot cost-utility analysis using quality-adjusted life years (QALYs) gained based on the answers to the EQ-5D-5 L. Additionally, since there is limited evidence on how the GHQ-12 and EQ-5D-5 L relate to each other [38], we will use the pilot data to explore the correlation of these two instruments in terms of health gains in different domains.

With the pilot cost and outcome data, we will explore the calculation of confidence intervals for costs and health gains using non-parametric bootstrapping, with the understanding that low numbers preclude generalisability. Also, we will explore the application of probabilistic sensitivity analysis that will eventually generate cost-effectiveness acceptability curves in a Phase III RCT. These curves graphically represent provisional estimates of the cost-effectiveness of the intervention.

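### Comparing mean-imputed with complete-case economic results cannot show whether missing data cause bias, and bootstrap intervals from once-filled data would be too narrow

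*Protocol article*

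**What the plan says.** The Missing data section treats the two parts of the trial differently. Clinical outcomes go into mixed models fitted by maximum likelihood under missing at random, with baseline predictors of missingness added. For the health-economic data, "we will analyse the data on a complete case analysis basis and additionally use mean imputation for missing values". The article then gives the purpose: "This will allow for a sensitivity analysis indicating whether missing values could be biasing the data".

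Under Economic evaluation analysis, "we will explore the calculation of confidence intervals for costs and health gains using non-parametric bootstrapping". Health gains there come from both the GHQ-12 and the EQ-5D-5L. The same section calls the economic work a very small exercise for finding data-collection problems and for developing the model to be used in a phase III trial.

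The only loss rate in the article is under Sample size: 60 recruited, 30 per arm, with about 15% lost, so that after allowing for the "lost to follow-up rate, at least 50 will complete the study". No missing rate is given for the CSRI or the EQ-5D-5L.

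**The concern.** The article fixes both a method and what the method is for, and the method cannot serve that purpose. Mean imputation takes its values from the people who were observed, so it holds no information on how the missing people differ from them. If the two analyses agree, the natural reading is that missing data did no harm, yet both may carry the same bias.

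Both analyses in general need data missing completely at random. That is a stronger and less plausible assumption than the missing-at-random assumption used for the clinical outcomes. The GHQ-12 falls under both: it is the primary clinical outcome and also an economic effect measure.

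Selective missingness is foreseeable here. Patient-reported outcome measures expects some GHQ-12 data to be lost through severe aphasia. Procedures makes the significant other the main CSRI respondent where there is one, while Significant others admits participants who have none. Mean imputation uses none of this.

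There is also a question of precision. Filled-in means are constants, and if they are resampled as though observed, the bootstrap understates the uncertainty.

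**Working it through.** **The plan's own figures.** 60 × 0.85 = 51, which agrees with at least 50 completers. Exactly 50 means 25 of 30 per arm, a loss of 10/60 = 16.7%. With 25 per arm and a standardised effect of 0.8, power is 80.7% (normal approximation) or 79.1% (noncentral t), so the stated 80% is reproduced. None of this is in dispute; it supplies n = 30 and m = 25 observed per arm. The second scenario, m = 21 (30% missing), is an assumption.

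**Step 1: arm-mean imputation of a total.** Let ȳ be the observed mean in an arm. After filling in, the arm mean is [mȳ + (n − m)ȳ]/n = ȳ. The difference between arms therefore equals the complete-case difference under any missingness mechanism.

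**Step 2: overall-mean imputation.** Let p = m/n in both arms and Y be the overall observed mean. Each arm mean becomes pȳ + (1 − p)Y, so the difference becomes p(ȳ₁ − ȳ₀): × 0.83 at 25/30 and × 0.70 at 21/30. The shift depends on how many people are missing, not on who they are.

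**Step 3: precision if means are filled in once.** Imputed values add nothing to the sum of squares, so the variance becomes s²(m − 1)/(n − 1) and the apparent standard error s√[(m − 1)/(n − 1)]/√n. The estimate is still ȳ, whose complete-case standard error is s/√m. The ratio is √[m(m − 1)/(n(n − 1))], and approximate coverage of a nominal 95% interval is 2Φ(1.96 × ratio) − 1.

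- m = 25: √(600/870) = 0.830; coverage 89.6%.
- m = 21: √(420/870) = 0.695; coverage 82.7%.

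A bootstrap standard error uses divisor n instead of n − 1, which makes the ratio m/n: 0.83 and 0.70.

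**Step 4: simulation.** Skewed two-period costs, 30 per arm, true difference 0, 2,000 replicates, percentile bootstrap. Under selective missingness, people in one arm with high costs were more often missing at the second period; the other arm lost people at random. Bias is in simulated cost units; the mean total is 2.5 × exp(0.8²/2) = 3.44.

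| 15% baseline missingness | Complete case | Arm mean of total | Each period imputed |
|---|---|---|---|
| Completely at random | −0.022 | −0.022 | −0.023 |
| At random, selective | −0.233 | −0.233 | −0.104 |
| Not at random, selective | −0.231 | −0.231 | −0.173 |

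The true bias in the first row is 0, so −0.022 shows the simulation noise. In the selective rows complete case and arm-mean imputation agree to rounding error (largest gap about 3e-15) while both are wrong by about 7% of mean cost (0.23/3.44).

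Period-level imputation does move the estimate, because it uses first-period costs of people missing later. The movement is a poor guide to the bias left. When data are missing at random the estimate moves 0.233 − 0.104 = 0.129 and 0.104 remains. When they are not, it moves only 0.231 − 0.173 = 0.058 and 0.173 remains.

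With data missing completely at random, intervals from once-filled data were 0.85 times the complete-case width at 15% missing (coverage 87.0% against 93.0%) and 0.70 times at 30% (77.4% against 91.4%). When imputation was redone inside each resample, the width ratio at 15% was 1.01, so the narrowing disappeared.

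**The case against.** The strongest reply is that nothing in the trial rests on these intervals. The article says low numbers preclude generalising, it only undertakes to explore the bootstrap, and the Discussion sets no targets for the feasibility outcomes. This stands, and it limits the severity.

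Three stronger readings are tempting, and the document does not support them.

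- A reader might infer that all the cost and QALY intervals will be too narrow. Complete-case intervals are not affected. The article does not say that the bootstrap is run on imputed data, or in which order, and re-imputing inside each resample removes the problem. The full protocol, which is not shown, may settle this.
- A reader might infer that the comparison will always look reassuring. That holds for arm means of a total. Overall-mean and period-level imputation can both produce a visible change, and period-level imputation does show something about dropping partial completers. The article does not fix the level.
- A reader might infer that missingness is not otherwise examined. Amounts and reasons will be summarised by arm, baseline characteristics of those with and without follow-up will be compared, and missingness of the primary outcome will be modelled. These help, but they do not estimate bias in costs or QALYs.

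Nor does the article say that cost or QALY standard deviations from this trial will be carried into the phase III model.

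What remains is that the stated purpose is wrong under every way of doing mean imputation considered here. That is a stated rule, not a detail left to a fuller document.

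**Conclusion.** The point holds. The claim that complete-case analysis plus mean imputation can indicate bias is wrong, whichever mean is imputed: the point estimate changes by exactly 0 (arm mean of a total), by a factor set by the observed share (overall mean, 0.83 at 25 of 30), or by an amount that does not track the bias (by period or item).

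The loss of precision is conditional. It applies to mean-imputed intervals when means are filled in once before resampling: standard error × 0.83 and coverage about 90% with 25 of 30 observed per arm, × 0.70 and about 83% with 21 of 30. The first case applies the trial's overall loss to the economic data; the second is assumed. The coverage figures use a normal approximation, and simulated coverage with skewed costs was lower.

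Severity is moderate or lower, because the evaluation is exploratory. It still merits correction: its declared aims are to find data problems and to develop the phase III economic model, and an unsound missing-data check could be carried over with that model.

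**What to change.** Replace mean imputation with multiple imputation under missing at random, done separately by arm and combined with the bootstrap so that the intervals carry the imputation uncertainty. Keep complete case as the comparator. Add one simple shift of the imputed costs and QALYs as the missing-not-at-random check; this is the part that can show how far the result depends on who is missing.

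Keep the predictors few: for example baseline EQ-5D-5L, baseline GHQ-12, aphasia severity, and observed 4-month cost and utility. With severity as one continuous score that is 1 + 5 = 6 coefficients, against 21 to 25 observed people per arm. Adding DISCS, recruitment area and wheelchair use, with severity in three levels, would make about 11, too many for these numbers. The CSRI is collected only at 4 and 10 months, so there is no baseline cost to use.

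The minimum change is to delete the sentence claiming that the comparison indicates bias, and to report no bootstrap intervals from singly mean-imputed data.

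The cost is a few lines of text and modest analyst time, with no new data. Intervals will be wider than the mean-imputed ones, and even a sparse imputation model will be somewhat unstable at this sample size, which should be said when the results are reported.
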